## Abstract

**Background:**

Depression is a global health challenge. Prevention is highlighted as a priority to reduce its prevalence. Although effective preventive interventions exist, the efficacy and coverage can be improved. One proposed means to increase efficacy is by using interventions to target specific risk factors, such as rumination. Rumination-focused CBT (RFCBT) was developed to specifically target depressive rumination and reduces acute depressive symptoms and relapse for patients with residual depression in a randomised controlled trial. Preliminary findings from a Dutch randomised prevention trial in 251 high-risk 15- to 22-year-old subjects selected with elevated worry and rumination found that both supported internet-RFBCT and group-delivered RFCBT equally reduced depressive symptoms and the onset of depressive cases over a period of 1 year, relative to the no-intervention control.

**Methods/Design:**

A phase III randomised controlled trial following the Medical Research Council (MRC) Complex Interventions Framework will extend a Dutch trial to the United Kingdom, with the addition of diagnostic interviews, primarily to test whether guided internet-RFCBT reduces the onset of depression relative to a no-intervention control. High-risk young adults (aged 18 to 24 years), selected with elevated worry/rumination and recruited through university and internet advertisement, will be randomised to receive either guided internet-RFCBT, supported by clinical psychologists or mental health paraprofessionals, or a no-intervention control. As an adjunct arm, participants are also randomised to unguided internet-RFCBT self-help to provide an initial test of the feasibility and effect size of this intervention. While participants are also randomised to unguided internet-RFCBT, the trial was designed and powered as a phase III trial comparing guided internet-RFCBT versus a no-intervention control. In the comparison between these two arms, the primary outcomes are as follows: a) onset of major depressive episode over a 12-month period, assessed with a Structured Clinical Interview for Diagnosis at 3 months (post-intervention), 6 months and 15 months after randomisation. The following secondary outcomes will be recorded: the incidence of generalized anxiety disorder, symptoms of depression and anxiety, and levels of worry and rumination, measured at baseline and at the same follow-up intervals. In relation to the pilot investigation of unguided internet-RFCBT (the adjunct intervention arm), we will assess the feasibility and acceptability of the data-collection procedures, levels of attrition, effect size and acceptability of the unguided internet-RFCBT intervention.

**Discussion:**

Widespread implementation is necessary for effective prevention, suggesting that the internet may be a valuable mode of delivery. Previous research suggests that guided internet-RFCBT reduces incidence rates relative to controls. We are also interested in developing and evaluating an unguided version to potentially increase the availability and reduce the costs.

**Trial Registration:**

Current Controlled Trials ISRCTN12683436. Date of registration: 27 October 2014

**Electronic supplementary material:**

The online version of this article (doi:10.1186/s13063-015-1128-9) contains supplementary material, which is available to authorized users.

## Background

Depression is one of the leading causes of disease burden worldwide, with substantial individual, societal and economic impact [1]. Current treatments have only a limited impact on this disease burden because of the lack of treatment availability, the high proportion of patients failing to respond (40 %, including partial and non-response) and the high levels of relapse or recurrence (50-80 %) [2]. In addition, treatments provided in the acute phase of the disorder do not reduce the incidence rates. Effective preventive interventions are therefore needed to reduce the disease burden of depression.

Preventive interventions for depression have mainly focused on children and adolescents and have predominantly used CBT strategies. Meta-analyses [3–5] have found that universal interventions (aimed at entire populations, regardless of risk factors) had only small-to-insignificant effect sizes post-intervention and longer-term effects were mixed. Greater effect sizes were found for targeted interventions (selective: aimed at a subgroup presenting with known risk factors; indicated: aimed at individuals with subclinical symptoms), and these effects were sustained for longer than universal interventions [5]. Critiques of prevention research trials include a focus on treatment effects (change in symptoms relative to controls [3]) rather than on a reduction in incidence rates [6]; insufficient statistical power due to low base-rates (particularly in universal samples); and short follow-up periods, which interfere with the elucidation of longer-term effects [5].

While there are some early positive findings from prevention research, improvement is possible in terms of efficacy, cost-effectiveness and acceptability [7]. First, interventions should be targeted at higher-risk individuals rather than at universal populations [7]. Such individuals have the most to gain from an intervention, and the base rate of new cases will be higher in high-risk groups, meaning that smaller sample sizes are needed to obtain adequate statistical power to detect an effect [6]. Such individuals could be identified on the basis of personal and familial history, cognitive or biological vulnerabilities to depression, and/or subsyndromal symptoms. Risk factors can be used not only to identify individuals but also as a direct target for intervention [7]. Additionally, although current interventions are largely aimed at specific disorders, evidence is increasing for transdiagnostic processes, which are risk factors for multiple disorders [8, 9]. Targeting such processes has the potential to impact several disorders with a single intervention [10].

Repetitive negative thought (RNT), incorporating worry and rumination, has been proposed as a potential target for selective prevention programmes [7]. Strong evidence exists that RNT contributes to the onset and maintenance of a range of disorders, including depression, anxiety and physical health issues [11]. Prospective longitudinal studies have found that rumination predicted a) future depressive symptoms, even after controlling for baseline depressive and anxious symptoms, across a range of follow-up periods [12–15]; b) onset and duration of episodes of major depression [16–19]; and c) mediated the effects of other risk factors on the onset of depression [20]. Rumination and worry have also been found to predict future levels of other disorders, including anxiety, eating disorders and substance abuse [18]. Furthermore, experimental studies provide evidence that rumination causally influences negative mood and a range of cognitive processes [11], including increased negative thinking [21], impaired concentration [22] and impaired problem-solving [23]. This relationship between RNT and emotional disorders is also found in children and adolescents [12, 18, 24–26]. Moreover, Hankin [27] demonstrated that rumination is a specific risk factor for depression in adolescence, with rumination prospectively predicting fluctuations in depressive symptoms and internalising problems, but not anxious arousal or externalising problems. A gender bias exists in depression rates (approximately 2:1 female: male [28]). Differences in rumination levels can partially explain this gender bias, with 27 % of the association between gender and depression explained by rumination [27]. Critically, recent experimental and clinical studies have shown that with brief interventions, levels of rumination and worry can be reduced (e.g. [29–33]). This suggests that rumination/worry could be a particularly promising target in improving the efficacy of preventive interventions.

Widespread dissemination and coverage of interventions is important for effective prevention. Traditional face-to-face therapy is not well-suited for such widespread implementation. Alternative modes of delivery, such as internet-based treatments, have potential advantages including the following: reaching large numbers at a relatively low cost; greater ease of access and convenience for the user; available at any time and place; and greater autonomy for the client, anonymity and greater time to reflect [6, 34, 35]. Emergent evidence exists that internet-based CBT is an effective, feasible and acceptable treatment for acute depression and anxiety [36, 37]. Acceptability ratings for internet-based therapies are generally high [35]. However, difficulties with motivation and adherence are a potentially important issue for Internet-based therapies for depression. Although purely self-guided internet interventions for depression are available, they are generally less effective and have greater drop-out than guided interventions for depression with therapist input [36, 38, 39]. Andersson [34] therefore argued for some form of guidance in order to achieve similar effectiveness to face-to-face therapies.

The feasibility, acceptability, and efficacy of internet-based rumination-focused CBT (i-RFCBT) to prevent depression in adolescents and young adults has recently been investigated in the Netherlands (Topper, Emmelkamp, Watkins and Ehring: Prevention of anxiety disorders and depression by targeting excessive worry and rumination in adolescents and young adults; A randomized controlled trial. Submitted; ZonMw funded project). The intervention is based on rumination-focused cognitive behavioural therapy (RFCBT) developed by Watkins et al. [30, 32]. Watkins et al. [32] conducted a randomised-controlled trial comparing treatment-as-usual (TAU, antidepressant medication) versus TAU plus RFCBT in patients with medication-refractory residual depression. The addition of RFCBT reduced depressive symptoms more than medication alone, with improvements in remission rates (62 % vs. 21 %) and reduction in 5-month relapse rates (9.5 % vs. 53 %) Moreover, changes in rumination scores were found to be a significant mediator of these treatment effects. These positive treatment and relapse prevention results led Topper et al. to adapt this intervention for prevention.

In a prevention trial of RFCBT, 251 students aged 15-22 with elevated worry and/or rumination (scoring on top quartiles of respective measures: ≥ 50 on Penn State Worry Questionnaire (PSWQ; [40]; ≥ 40 on Ruminative Response Scale of the Response Styles Questionnaire (RRS; [15])) but who did not currently meet diagnostic criteria for depression or generalized anxiety disorder were recruited, and randomised into face-to-face group RFCBT, internet-delivered RFCBT (i-RFCBT), or a no-intervention control group. Participants were assessed for symptoms and ‘caseness’ of depression and anxiety on standardised self-report measures (Patient Health Questionnaire, PHQ-9; [41]; Generalized Anxiety Disorder Screener, GAD-7; [42]) at baseline, post-intervention, 3 month and 12 month follow-ups. This study indicated the feasibility of recruiting and retaining participants for such a prevention study and indicated the acceptability of these interventions. Further, group RFCBT and internet RFCBT reduced worry, rumination, depression and anxiety symptoms significantly more than waiting list control. At 12 month follow-up, cumulative incidence rates for depression (estimated from “caseness” on PHQ-9) are reduced in the two RFCBT intervention groups (13.1 %) relative to controls (32.2 %). Moreover, reductions in rumination and worry were found to mediate the effects of RFCBT on symptom severity.

These findings are encouraging. However, there are several key limitations of the Dutch study: (a) there is not a diagnostic interview to determine incidence of major depression, with the study instead using self-report and only able to assess point prevalence rather than retrospective incidence; (b) similarly, it is not known whether the participants had previous episodes of depression, i.e., whether the intervention prevents first onset or relapse/recurrence of depression.

### Study aims and objectives

The primary aim of this phase III efficacy trial is to replicate and extend the Dutch study to compare guided i-RFCBT with a no-intervention control. If the target sample size based on the comparison of guided i-RFCBT to controls in the Dutch trial is achieved, the aim is to assess whether the findings from this previous trial can be replicated in a different population of undergraduates in the United Kingdom.

The RESPOND study will address the limitations of the Dutch trial by including a well-validated diagnostic interview (Structured Clinical Interview for DSM-IV (SCID-I [43]) to increase accuracy in determining current and past diagnostic status, and to allow for stratification on history of depression. Although including previously depressed participants is not consistent with strict definitions of initial onset prevention studies, there is a strong argument for preventing further relapses and recurrences, especially as a major risk factor for a depressive episode is a history of depressive episodes [6].

One key change from the design of the Dutch trial is the selection of a young adult population aged 18-24-years, principally undergraduates, rather than 15-22 years-old, in order to recruit participants able to provide their own informed consent. This age group was chosen for a number of reasons: (a) for pragmatic reasons to improve feasibility and logistics of recruitment, since parental consent can be a barrier to recruitment for an internet-based prevention study [44]; (b) larger effect sizes are found for older adolescents in preventive studies, perhaps because older adolescents are better able to understand the intervention compared to younger adolescents or children [4] and c) life transitions such as moving out of the family home have been shown to increase the incidence of depression [45]. Additionally depression is prevalent in this population [46] and the number of students experiencing high levels of worry, stress and symptoms of depression and anxiety is also high [47], indicating that there is a significant group of at-risk students who could be targeted with a preventive intervention.

While previous research suggests guided interventions are more efficacious than unguided interventions, making the study of guided i-RFCBT our primary goal, clinically relevant benefits could still be obtained with unguided interventions as these have the potential to be accessed by larger numbers at a lower cost, and are essential for making highly scalable interventions. As a quasi-phase II pilot arm, we will therefore also include an unguided version of i-RFCBT to pilot its feasibility. This inclusion aims to assess the feasibility of retention and acceptability of the unguided intervention, as well as to estimate its effect sizes and variability to aid planning for a fully powered definitive trial of the unguided version, with respect to rates of incidence and levels of symptoms (descriptives and confidence intervals), as a separate analysis from the primary Phase III design.

## Methods/Design

### Study Design

#### Phase III efficacy study

The phase III study will consist of a single (researcher) blind parallel-group randomised-controlled trial (RCT), comparing guided i-RFCBT versus a no-intervention control group, with this our primary research question.

#### Quasi-Phase II pilot arm

A separate adjunct arm of unguided i-RFBCT will be included as a quasi-phase II pilot arm to enable a feasibility study of this intervention. This will be a separate question, and there will be no direct comparison between unguided i-RFCBT and the guided i-RFCBT or control arms in the phase III efficacy study.

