### Randomisation and allocation concealment

Independent computer-generated block randomisation to the guided i-RFCBT, unguided i-RFCBT or the no-intervention control group will be used. Randomisation will be stratified by sex and by past history of depression (presence or absence of past depressive episodes) to assess the effect of sex on outcomes and to examine potential differences between prevention of first onset and relapse prevention. The randomisation uses blocks of three to ensure close parity of randomisation across the intervention arms across time. Because of the two levels of stratification by sex and by level of depression, with blocks of three, the researcher would not be able to anticipate or determine allocation easily, and the use of varying block sizes was therefore deemed unnecessary. In order to preserve blinding of the study researcher, randomisation will be conducted by a third party not involved in assessing or treating the participants, and this third party will also inform the therapist, who will be responsible for informing participants of their allocation.

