### Sample for quasi-phase II pilot arm

In the absence of any data on the unguided i-RFCBT, no power and sample size calculation was conducted for this arm. We will therefore aim to recruit the same number of participants for this arm as the other arms (n = 78), giving a total sample size of 234. The inclusion of this intervention arm is to explore the feasibility of this unguided intervention with respect to attrition, acceptability and estimates of incident rate and effect size.

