### Feasibility and acceptability outcome measures (quasi-phase II pilot arm)

With respect to the unguided intervention, feasibility and acceptability of data collection procedures, levels of attrition, effect size and acceptability of the unguided internet RFCBT intervention will be measured to aid planning for a fully powered, definitive, phase III trial. The feasibility of data collection procedures will be assessed by measuring the missing items on the clinical outcome measures, the number and timing of drop-outs and whether these vary across arms. The acceptability of the intervention will be assessed using a behavioural index, which will measure the number of modules completed, the time spent logged into the site and which modules are completed more easily or frequently than others.

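### The unguided arm is meant to supply an effect size for planning a definitive trial, but the plan says it will not be directly compared with the control arm and names no other contrast

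*Protocol article*

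**What the plan says.** The section Quasi-Phase II pilot arm treats the unguided intervention as a separate question and adds that "there will be no direct comparison between unguided i-RFCBT and the guided i-RFCBT or control arms in the phase III efficacy study".

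Other sections of the protocol article give the arm these purposes:

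- Abstract, Methods/Design: "participants are also randomised to unguided internet-RFCBT self-help to provide an initial test of the feasibility and effect size of this intervention".
- Study aims and objectives: to "estimate its effect sizes and variability to aid planning for a fully powered definitive trial of the unguided version". The same sentence confines the output to incidence and symptom figures, given descriptively with intervals and kept apart from the phase III analysis.
- Sample for quasi-phase II pilot arm: feasibility in terms of "attrition, acceptability and estimates of incident rate and effect size".
- Feasibility and acceptability outcome measures: effect size is listed again as an input to a later definitive trial, and data collection is to be judged partly by "the number and timing of drop-outs and whether these vary across arms".

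Allocation is concurrent: "Independent computer-generated block randomisation to the guided i-RFCBT, unguided i-RFCBT or the no-intervention control group will be used". It is stratified and uses blocks of three, and 78 participants are planned for each arm.

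**The concern.** An effect size that is to size a randomised trial has to be a contrast with a comparator. The article uses the term that way itself: its sample size section works from a hazard ratio of 0.41 between guided i-RFCBT and control, and from d = 0.51 for symptom change relative to a waiting-list control. For the unguided arm it promises an effect size, declares that there will be no direct comparison, and names no other contrast.

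Two analysts could both claim to follow this text and report different things. One would give the incidence rate and symptom levels in the unguided arm alone. The other would give an unguided-versus-control estimate. Only the second can be carried into the design of a definitive trial as an effect. If the first is reported and read as an effect, the next trial may be sized on a figure that partly reflects what would have happened without the intervention.

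**Working it through.** **1. The plan's own figure.** For d = 0.51, two-sided 5% and 80% power, the t-test calculation needs 61.3, so 62 per arm. Allowing for 20% drop-out, 62/0.8 = 77.5, so 78. Three arms give 3 × 78 = 234. The stated sizes reproduce, and 62 is the expected number of completers per arm.

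**2. What the literal reading delivers.**

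- *Incidence.* Current major depressive episodes are excluded (Participant exclusion criteria), so the baseline rate is zero by design. The unguided arm alone gives a cumulative incidence. At an assumed 20% with 62 completers, its 95% half-width is 1.96 × √(0.2 × 0.8/62) = 0.10. That describes a rate and says nothing about prevention.
- *Symptoms.* The arm alone gives levels or a change over time. No section plans a pre-post estimate. If one were used for want of a comparator, it would include natural course and selection effects.

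**3. How large selection effects could be.** The documents give no test-retest or between-scale correlations, so everything in this step is assumed. Scores are taken as normal with SD 1 and test-retest correlation r.

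- *A single cut at the 75th percentile.* The mean above the cut is φ(0.6745)/0.25 = 1.27 SD. The expected untreated fall is 1.27 × (1 − r): 0.51 SD at r = 0.6 and 0.25 SD at r = 0.8. This is not the trial's rule.
- *The trial's rule: above the cut on at least one of worry and rumination.* Let ρ be the correlation between the two scales and P the fraction selected. The mean on each scale is m = (1 + ρ) × φ(c) × Φ(c√((1 − ρ)/(1 + ρ)))/P, with c = 0.6745. For ρ = 0.4, P = 0.393 and m = 0.76; for ρ = 0.55, P = 0.373 and m = 0.85.
  - If measurement errors on the two scales are independent, the fall is (1 − r)m/(1 + ρ): about 0.22 SD at r = 0.6, 0.11 at 0.8 and 0.05 at 0.9.
  - If the scales share their errors on an occasion, the fall is (1 − r)m: 0.30 to 0.34 SD at r = 0.6 and 0.15 to 0.17 at r = 0.8.
- *Depressive symptoms.* High scorers are removed (PHQ-8 of 15 or more at online screening, and current episodes at interview). Assume a correlation of 0.5 with each selection scale and a depression cut at +1.0 or +1.5 SD.
  - With independent errors, simulation for r from 0.6 to 0.9 gives an apparent untreated *rise* of about 0.03 to 0.23 SD.
  - With shared errors, the mean depression score after selection is about 0.10 or 0.31 SD. The fall, (1 − r) times that, is 0.01 to 0.12 SD.

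The sign for depressive symptoms therefore depends on the assumptions.

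**4. What the randomised contrast would deliver.**

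- *Standardised mean difference, 62 per arm.* 1.96 × √(2/62) = ±0.35. Adding the term for d = 0.51, 1.96 × √(2/62 + 0.51²/(4 × 62)) = ±0.36. With all 78 per arm the second formula gives ±0.32.
- *Cumulative-incidence difference.* Assume 32.2% in control and, for illustration, 13.1% in the unguided arm. Then 1.96 × √(0.322 × 0.678/62 + 0.131 × 0.869/62) = ±14.3 points, or ±12.8 points with 78 per arm.

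**The case against.** The best defence is that the bar is limited. It can be read as applying only inside the phase III efficacy study, which the article defines as guided i-RFCBT versus control. The study aims place the unguided estimates in a separate analysis with descriptives and confidence intervals, and the interest in whether drop-out varies across arms shows that cross-arm looks are not banned altogether. The article is also condensed, so the pilot contrast and model could properly sit in a fuller document.

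Part of this stands. The text does not clearly forbid every comparison, and leaving the model to an analysis plan would be no fault. But the unguided arm is not part of the phase III study, so the limiting phrase reads more naturally as describing the arms it is not to be compared with. Even on the lenient reading, the study aims offer rates of incidence and levels of symptoms and name no contrast. The point is not a missing detail: a stated restriction collides with a stated aim.

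A reader might go further and infer that only a pre-post change is left, and that regression to the mean will inflate it by about as much as the planned d = 0.51. The documents do not support that. No section plans a pre-post analysis. The 0.25 to 0.51 SD range belongs to a single cut, not to the either-of-two rule. And d = 0.51 concerns depressive symptoms, for which high scorers are excluded and the bias may run either way.

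**Conclusion.** The point holds as an inconsistency between the stated restriction and the stated purpose of the unguided arm. Taken literally, the plan yields single-arm figures that cannot serve as an intervention effect, although a concurrently randomised control arm of the same planned size is available. That conclusion follows from the text and needs none of the assumed correlations. Those show only that an uncontrolled symptom change could be off by an amount, and for depressive symptoms in a direction, that the documents cannot settle.

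The randomised estimate would be imprecise: about ±0.35 to ±0.36 SD with 62 completers per arm, assuming the 20% loss on which the plan relies. That suits an exploratory planning estimate and not a claim of efficacy. The matter should be corrected because it affects a stated aim of the third arm. It does not touch the guided-versus-control comparison.

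**What to change.** Reconcile the section Quasi-Phase II pilot arm with the Abstract, the study aims, the pilot-sample section and the pilot outcome section. Suggested content: no hypothesis test will compare the unguided arm with the guided or control arms. The pilot effect size is the randomised unguided-versus-control estimate, labelled exploratory and given with 95% CIs, as a hazard ratio or cumulative-incidence difference for major depressive episode and as baseline-adjusted mean differences for symptoms. Drop-out will be described by arm.

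The cost is a change of wording and one extra exploratory table with wide intervals, which should be presented so that it is not read as a test of efficacy. No further recruitment is needed, and the primary comparison, alpha and sample size stay as they are.
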